## Abstract

**Introduction::**

Henoch–Schönlein purpura nephritis (HSPN) involves the renal impairment of Henoch–Schönlein purpura and can easily relapse into life-threatening late nephropathy in severe cases. Although there is a lack of validated evidence for its effectiveness, Chinese herbal medicine (CHM) is one of the most commonly used methods in China to treat HSPN. It is thus need to report the protocol of a prospective cohort trial using CHM to investigate the effectiveness, safety and advantages for children with HSPN.

**Methods and analysis::**

This large, prospective, multicenter cohort study started in May 2015 in Shenyang. Six hundred children diagnosed with HSPN were recruited from 3 institutions and are followed-up every 2 to 4 weeks till May 2020. Detailed information of participants includes general information, history of treatment, physical examination, and symptoms of TCM is taken face-to-face at baseline.

**Ethics and dissemination::**

This study has received ethical approval from the ethics committee of institutional review board of the Affiliated Hospital of Liaoning University of Traditional Chinese Medicine (No.2016CS(KT)-002-01). Articles summarizing the primary results and ancillary analyses will be published in peer-reviewed journals.

**Trial registration::**

Clinical Trials Registration: NCT02878018.

## Introduction

1

Henoch–Schönlein purpura (HSP) is a systemic disorder characterized by leukocytoclastic vasculitis involving the capillaries and deposition of IgA immune complexes.^[1]^ The ages of more than 90% of HSP patients are <10 years.^[2,3]^ Epidemiological studies have shown that Asians have a relatively higher incidence rate of HSP than Caucasians and Africans.^[2]^ Kidney injury, which is called Henoch–Schönlein purpura nephritis (HSPN), is one of the major manifestations and the primary cause of mortality from HSP.^[1]^ During the 4 to 6 weeks of initial disease presentation, approximately 40% of children with HSP progress to HSPN.^[4,5]^ Persistent purpura, severe abdominal symptoms, and an older age are 3 of the strongest risk factors for HSPN.^[6]^ Great efforts are needed to control the kidney injury for children with HSP who are at an increased risk of renal insufficiency.

However, therapies of Western medicine (WM) for HSPN, including corticosteroids, immunosuppressive treatment, and anticoagulant therapy, have the potential to cause adverse side effects and remain controversial.^[7–9]^ A clinical study demonstrated that early corticosteroid therapy does not prevent delayed nephritis in children with HSP.^[10]^ Immunosuppressive agents including cyclophosphamide have side effects such as oncogenesis, myelosuppression, hemorrhagic cystitis, and interstitial pneumonia.^[11,12]^ Moreover, the symptoms may recur easily after a long duration of treatment. Effective treatment for improving the long-term clinical management of HSPN remains an urgent need.

In China, the majority of HSPN patients resort to Chinese herbal medicine (CHM), acupuncture, and other traditional Chinese medicine (TCM) therapies.^[13,14]^ In TCM, HSPN is categorized as “purpura” or “hematuria.” In recent years, quite a few trials conducted in China have suggested that the use of CHM in conjunction with corticosteroids or immunosuppressive drugs generated additional positive effects,^[15–20]^ such as relieved blood hypercoagulable state, reduced proteinuria, and improved TCM signs and symptoms. These results indicated a potential role for CHM in the combined, consolidate, and maintenance treatment of HSPN. In this trial, we intend to assess the efficacy and advantage of the use of CHM for the treatment of children with HSPN.

## Methods and analysis

2

### Study design

2.1

This large, prospective, multicenter cohort study is being conducted in 3 institutions between May 2015 and May 2020. Six hundred participants are recruited and divided into 2 cohorts, with 300 individuals per cohort. All cohorts will undergo a 12-week treatment and a 12-month follow-up period. Participants will be asked to visit the clinicians every 2 weeks during the treatment period and once a month during the follow-up period. The feasibility and preciseness of the whole process are supervised by 1 to 2 supervisors.

### Study settings and participants

2.2

HSPN patients are being recruited from outpatient and inpatient departments of three large comprehensive hospitals in China, including the Affiliated Hospital of Liaoning University of TCM, the First Affiliated Hospital of China Medical University, and the Shengjing Hospital of China Medical University. The patient screening will be conducted by clinicians who are not involved in the study. If a patient meets the study criteria, the clinician who is responsible for the patient screening will provide him/her with written information, explain the study in detail in an understandable language and obtain the written consent if he/she is willing to take part in the study. Informed consent must be obtained for all patients enrolled in the study. The eligible children with HSPN taking CHM in one of the above 3 hospitals were classified as cohort 1 and participants received WM without CHM belong to cohort 2. Trials that combine CHM with WM will be included, if the cohort 2 received the same WM as the cohort 1. Doctors of traditional Chinese medicine in the above hospitals prescribe CHM for patients according to their symptoms and signs, tongue manifestations, and pulse condition. The study flow chart is shown in Figure 1.

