#### Exclusion criteria

2.4.3

1.HSPN with renal insufficiency.2.A clinical classification of HSPN that includes nephritic syndrome, rapidly progressive glomerulonephritis, and chronic glomerulonephritis.3.Suffering from serious complications, such as respiratory, digestive, hematological, or liver diseases.4.Tumor, infectious diseases, or mental disorders.5.Allergic to TCM use.6.No prescribed medication, poor compliance, or incomplete data affecting the efficacy and safety of these judgments.7.A history of another clinical trial in the previous 2 weeks.8.No consent form signed.

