### Data collection

2.8

Both cohorts undergo a 12-week treatment and 12-month follow-up. Case report forms (CRFs) contain a range of information, and these will be completed by the corresponding researchers at each center. The recruited patients will be asked to visit the clinicians 7 times for the assessment of the treatment efficacy during the treatment period (at baseline and in the 2nd, 4th, 6th, 8th, 10th, and 12th weeks after the first treatment). During the follow-up period, patients will be asked to visit once a month. If a patient fails to visit during one of the follow-up observations, the assessor will contact him/her by phone (Table 2). All data collected using paper-based CRFs will be submitted to an online clinical research data-capture computer system developed by the research group (http://59.46.50.9:9889). Only the members from the research team will have access to these data.

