### Statistical analysis

2.9

The statistical analysis will be conducted by a statistician of the Institute of Basic Research in Clinical Medicine, China Academy of Chinese Medical Sciences, Beijing, China. The statistician is blinded to the entire trial and will use SAS 9.1.3 (SAS Institute, Cary, NC, USA) and SPSS Version 13.0 (SPSS Inc., Chicago, IL) software. To test the hypotheses about associations between baseline risk factors and HSPN incidence, hazards ratios will be computed using the Cox proportional hazard regression models. Baseline differences between the groups will be assessed with the use of Student's *t*-test for normally distributed continuous variables and the nonparametric Mann–Whitney *U*-test for non-normally distributed variables. Comparisons between the groups will be conducted using an analysis of covariance (ANCOVA) with the baseline as the covariate. For efficacy analysis, changes from the baseline to the endpoint of treatment in scores will be tested with repeated measured analysis of variance (ANOVA). Within each group, differences will be assessed with paired t-test for normally distributed data and the Wilcoxon signed-rank test for non-normally distributed data. Safety will be assessed by participant compliance and adverse events. For analysis of the final dataset, missing data will be filled in using the last observation carried forward (LOCF) approach. A *P* value <.05 is considered significant.

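### Neither the cohort definitions nor the eligibility lists require a new start of treatment or limit earlier CHM or WM use, so baseline may not be the start of treatment for every child

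*Protocol article*

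**What the plan says.** Section 2.2 assigns children by the treatment they receive, not by randomisation. Of the exposed cohort it says "The eligible children with HSPN taking CHM in one of the above 3 hospitals were classified as cohort 1"; of the comparator, "participants received WM without CHM belong to cohort 2". It also allows CHM combined with WM in cohort 1, provided that cohort 2 receives the same WM.

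The five inclusion and eight exclusion criteria (2.4.2, 2.4.3) are printed item by item. The only one with a look-back period is "A history of another clinical trial in the previous 2 weeks". The only one that mentions medication is "No prescribed medication, poor compliance, or incomplete data affecting the efficacy and safety of these judgments". None concerns CHM, corticosteroids or immunosuppressants taken in ordinary care before enrolment.

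The timetable is written as if treatment begins at baseline. Section 2.1 says "All cohorts will undergo a 12-week treatment and a 12-month follow-up period", and section 2.8 places the visits "at baseline and in the 2nd, 4th, 6th, 8th, 10th, and 12th weeks after the first treatment".

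Earlier treatment is recorded. The abstract says "Detailed information of participants includes general information, history of treatment, physical examination, and symptoms of TCM is taken face-to-face at baseline". The stated analysis does not use it; section 2.9 says "Comparisons between the groups will be conducted using an analysis of covariance (ANCOVA) with the baseline as the covariate".

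**The concern.** The visit schedule presupposes a time zero that the cohort definitions do not secure. The wording of 2.2 admits a child who has been on CHM or WM for some time as readily as one who starts at baseline. It also admits to cohort 2 a child who stopped CHM shortly before. The introduction says that most patients in China turn to CHM, acupuncture and other traditional therapies, so earlier exposure is plausible in both cohorts.

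Three things are at stake:

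- **Remission.** If children who did badly on CHM stopped before cohort 1 was formed, those left look better than new starters would. If some of them are now in cohort 2, the contrast widens. If the children still on CHM are the slow or resistant cases, the bias runs the other way.
- **Symptom scores.** A baseline already lowered by treatment leaves less room for change. In the analysis of covariance, the covariate is then itself affected by the treatment under study.
- **Adverse events.** Events early in a course begun before baseline fall outside the observation period.

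Without randomisation, nothing in the design balances time on treatment or earlier response between the cohorts.

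**Working it through.** **Setting the passages side by side**

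1. Does any criterion require a new start? No. Neither cohort definition in 2.2 and no item in 2.4.2 or 2.4.3 does.
2. Does any criterion limit earlier exposure? No. The 2-week look-back concerns trial participation only. The exclusion that mentions medication removes children without a prescription and says nothing about earlier users.
3. Does the schedule define time zero? Only by implication. Section 2.8 does not say whether the first treatment is the child's first ever or the first within the study.
4. Does a stated analysis use treatment history? No. Section 2.9 names the baseline value as the covariate and nothing else.

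**Illustration of size**

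The plan gives no share of earlier users and no carry-over size, so there is no figure of its own on this point to reproduce. From section 2.6 I take the 40% response in cohort 2, 300 recruited and 250 evaluable per cohort, and two-sided alpha 0.05. I assume:

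- p = share of cohort 1 already on CHM at baseline;
- d = difference in their remission probability from new starters, of either sign;
- no true effect of CHM, and no earlier CHM in cohort 2.

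The expected remission in cohort 1 is P1 = 0.40 + p·d. With P2 = 0.40 and mean P̄ = (P1 + P2)/2, the standard errors are SE0 = √[2·P̄(1−P̄)/n] under the null and SE1 = √[(P1(1−P1) + P2(1−P2))/n]. The chance of a significant result is approximately 1 − Φ[(1.96·SE0 − |P1−P2|)/SE1], plus the small opposite tail.

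Worked case, p = 0.30, d = +0.20, n = 300:

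- P1 = 0.46, P̄ = 0.43;
- SE0 = √(2·0.43·0.57/300) = 0.0404;
- SE1 = √[(0.46·0.54 + 0.40·0.60)/300] = 0.0404 (0.04035 before rounding);
- (1.96·0.04042 − 0.06)/0.04035 = 0.477, and 1 − Φ(0.477) = 0.317.

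| p | d (points) | P1 | n = 300 | n = 250 |
|---|---|---|---|---|
| 20% | +10 | 42% | 8% | 7% |
| 30% | +20 | 46% | 32% | 27% |
| 50% | +20 | 50% | 69% | 61% |
| 20% | −10 | 38% | 8% | 7% |
| 30% | −20 | 34% | 33% | 28% |
| 50% | −20 | 30% | 73% | 65% |

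The nominal value is 5%. Rows with positive d give false findings in favour of CHM; rows with negative d give false findings against it.

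Over a wider grid (p from 25% to 75%, d from 10 to 20 points in either direction), the spurious difference p·d runs from 0.25 × 10 = 2.5 to 0.75 × 20 = 15 points. The planned difference is 53 − 40 = 13 points.

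**The case against.** The strongest reply is that the document intends baseline to be the start of treatment. Section 2.2 describes screening, consent and classification. Section 2.1 says that all cohorts will undergo a 12-week course, and section 2.8 counts weeks from the first treatment. On this view, taking CHM simply names the treatment received in the study, in parallel with the wording for cohort 2. This stands as a statement of intent. It does not stand as a safeguard, because no criterion makes the first study treatment coincide with the start of CHM or WM.

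Four further points are fair:

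- The exclusion for no prescribed medication sits beside poor compliance and incomplete data, which arise after enrolment. It is no evidence that current users are sought.
- The introduction speaks of CHM together with acupuncture and other traditional therapies. It makes earlier exposure plausible but does not show it.
- Section 2.5.1 gives no time point for remission, so a 12-week remission comparison can only be inferred.
- Treatment history is collected, and an analysis plan that is not shown may use it. Figure 1 and Table 2 are also not shown. But eligibility and cohort assignment belong in the protocol, and this article prints its criteria in full. Adjustment for recorded history also cannot restore children who stopped CHM before cohort 1 was formed.

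**Conclusion.** The point holds as an unsecured time zero and unhandled earlier exposure. The criteria let children with earlier CHM or WM enter a non-randomised comparison, and the stated analysis takes no account of it. This should be fixed, but it does not by itself invalidate the study.

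A reader might infer more: that cohort 1 consists of children already on CHM, that baseline is therefore not the start of treatment, and that the comparison is tilted towards CHM. The document does not support this. Section 2.2 does not say that CHM began before enrolment, and 2.1 and 2.8 point the other way. The direction of bias depends on whether children on continuing treatment are responders or resistant cases, on which the document is silent.

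The size is equally open. Over the tabulated assumptions the chance of a false significant result runs from 7% or 8%, close to nominal, to about 70%. These figures rest wholly on the assumed p and d, and show only that moderate values would matter.

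**What to change.** - **Sections 2.2 and 2.8.** Define time zero as the first study treatment of the cohort's course, and say that the week counts run from it. From the treatment history taken at baseline, flag (a) children in either cohort already on their cohort's treatment and (b) cohort 2 children with earlier CHM. This can be done for children already enrolled.
- **Section 2.9.** Adjust the between-cohort comparisons for this earlier exposure or stratify by it. Pre-specify an analysis restricted to new starters without earlier CHM, presented alongside the full cohort, and report the flagged children separately.

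The cost is a wording change, modest extra analysis and wider intervals in the restricted set. If a share q were removed from both cohorts, the intervals would widen by a factor of about 1/√(1−q): 12% wider at q = 20%, 20% at 30% and 41% at 50%. The planned size has little to spare: the formula above, with 53% against 40% and 250 per cohort, gives about 83% power, not the stated 90%. That shortfall is a separate matter, but it is a reason to keep the full cohort, with adjustment, rather than make new starters the sole primary set.

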### Sample size calculation

2.6

According to the response rates of treatment, the cohort 1 and the cohort 2 were 53% and 40%, respectively. It was estimated that 250 patients of each group would be sufficient to achieve 90% power in detecting treatment differences, based on a 2-sided alpha at a significance level of 0.05. Meanwhile, considering a dropout rate of 20%, we concluded that a total of 300 patients for each cohort would need to be recruited to ensure significant results.

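### Cohort 1 may hold children on CHM alone and on CHM plus WM, and the only rule on co-treatment has no child-level meaning, so the one comparison can blend a replacement effect with an add-on effect.

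*Protocol article*

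**What the plan says.** Section 2.2 (Study settings and participants) defines exposure in two sentences. The first sets the cohorts: "The eligible children with HSPN taking CHM in one of the above 3 hospitals were classified as cohort 1", while "participants received WM without CHM belong to cohort 2". Concurrent WM is neither required nor ruled out for cohort 1. The second deals with combined treatment: "Trials that combine CHM with WM will be included, if the cohort 2 received the same WM as the cohort 1". Because combined treatment is admitted as a conditional case, the natural reading is that CHM without WM is admitted too.

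The rest of the article works with two groups. Section 2.1 (Study design) states: "Six hundred participants are recruited and divided into 2 cohorts, with 300 individuals per cohort". Section 2.6 (Sample size calculation) gives one response rate per cohort: "the cohort 1 and the cohort 2 were 53% and 40%, respectively". Section 2.9 (Statistical analysis) describes comparisons between the groups by analysis of covariance, and baseline is the only covariate it names.

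Two places in the Introduction bear on the meaning of the contrast. It lists "therapies of Western medicine (WM) for HSPN, including corticosteroids, immunosuppressive treatment, and anticoagulant therapy", so WM is not one regimen. It also cites earlier Chinese trials as suggesting that "the use of CHM in conjunction with corticosteroids or immunosuppressive drugs generated additional positive effects", which is evidence about add-on use. The stated aim, in the Introduction and again at the end of the article, is only to assess the use of CHM.

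**The concern.** Two different questions can sit inside one comparison. A child on CHM alone, set against a child on WM, tells us about replacing WM. A child on CHM plus WM, set against a child on the same WM, tells us about adding CHM. A pooled estimate is a weighted average of the two, and its weights come from what the doctors prescribed. Unless the two effects happen to be equal, the pooled figure answers neither question, and a different prescribing mix would give a different answer.

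The same-WM sentence looks like the safeguard, but it reads like a study-selection rule in a review of several trials. This study enrols individual children. A condition on what a whole cohort received does not tell a coordinator whether a given child on CHM plus a corticosteroid is eligible, when this is checked, or whether the same WM means the same class, drug or regimen. Even read generously as a matching rule, it does not cover children on CHM alone, who have no WM to match.

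At stake is what the trial can conclude. A real add-on benefit could be diluted by a weaker replacement effect, or a pooled difference could be read as an add-on benefit that is not there.

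**Working it through.** **Inputs from the article:** response 53% in cohort 1 and 40% in cohort 2, two-sided alpha 0.05, 90% power, 250 evaluable per cohort (section 2.6); two cohorts of 300 (section 2.1).

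**Inputs not in the article, so assumed:** q, the share of cohort 1 on CHM alone; A, the add-on effect (CHM plus WM minus WM); R, the replacement effect (CHM alone minus WM).

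**1. The plan's own figure.** With the pooled-variance formula for two proportions and mean response 0.465,

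n = [1.96 × √(2 × 0.465 × 0.535) + 1.2816 × √(0.53 × 0.47 + 0.40 × 0.60)]² / 0.13² = (1.3825 + 0.8963)² / 0.0169 = 307.3, so 308 per cohort.

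The stated 250 is not reproduced; at 250 the power is 83.2%. That is a separate matter. It enters here only because 83.2%, not 90%, is the starting point for step 3.

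**2. The pooled difference.** If 40% is the right comparator response for both kinds of cohort 1 child, then

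D = (1 - q) × A + q × R.

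Suppose, for illustration, A = +13 points (the whole planned difference given to add-on use) and R = -5 points:

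- q = 25%: 0.75 × 13 - 0.25 × 5 = 8.5 points
- q = 50%: 0.50 × 13 - 0.50 × 5 = 4.0 points
- q = 75%: 0.25 × 13 - 0.75 × 5 = -0.5 points

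With R = 0 (CHM alone equal to WM), the pooled differences are 9.75, 6.5 and 3.25 points. With R = +13, D is 13 points whatever q is, so there is no dilution.

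**3. Power for the pooled difference at 250 per cohort.** Power = Φ[(D - 1.96 × se0) / se1], with se0 the pooled and se1 the unpooled standard error.

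| Share on CHM alone | R = -5: D, power | R = 0: D, power |
|---|---|---|
| 25% | 8.5 points, 48% | 9.75 points, 59% |
| 50% | 4.0 points, 15% | 6.5 points, 31% |
| 75% | -0.5 points, sign reversed | 3.25 points, 11% |

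**4. The reverse direction.** A pooled 53% does not reveal its parts. At q = 50%, it fits add-on 60% with CHM alone 46% (0.5 × 60 + 0.5 × 46 = 53). It equally fits add-on 40%, which is no add-on effect, with CHM alone 66% (0.5 × 40 + 0.5 × 66 = 53).

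**5. What does not depend on assumptions.** The cohort definitions admit both kinds of child, the co-treatment rule has no child-level criterion, and the design and sample size sections carry a single cohort contrast.

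**The case against.** The strongest reply has four parts.

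*The mix is permitted, not stated.* This stands. Nothing in the article fixes the share on CHM alone, which could be zero or the whole of cohort 1. A reader might infer that cohort 1 does contain a substantial mixture; the text supports only that it may.

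*The sentence may be meant as matching or restriction.* This also stands. A reader might infer that the rule can never be met or enforced, but the article does not show that. The WM classes in the Introduction are for the disease in general. Section 2.4.3 excludes the more severe clinical types, so WM among enrolled children may be narrower. What remains is that the sentence does not say how it is to be applied.

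*The 53% belongs to cohort 1 as a whole.* Correct. If it is the expected response of the cohort as it will be recruited, the planned difference already includes any blend. A reader might infer from the table above that the trial loses that much power; the article does not support this, because giving the 13 points to add-on use is an assumption.

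*Care that includes CHM versus WM without CHM is a coherent pragmatic question.* Granted. CHM alone against WM is an ordinary active-comparator contrast, and pooling is not wrong in itself. A reader might also infer that CHM would be credited with the effect of co-given WM. Since every cohort 2 child has WM, that would need WM to differ between the cohorts, which the same-WM condition seems meant to prevent.

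The selection flow chart (Figure 1) is not shown, and an unseen analysis plan might adjust for concurrent WM. Neither would remove the ambiguity in the written exposure definition.

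**Conclusion.** The concern holds as a fault of definition. Section 2.2 lets cohort 1 contain CHM alone and CHM plus WM, and it controls co-treatment only through a condition on trials and cohorts that names no child and no standard of sameness. The single comparison can therefore mix replacement and add-on effects in proportions set by prescribing, and the intended contrast is not fixed.

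The article gives no basis for a size. The illustrative figures rest on an assumed mix, assumed effects and a common comparator response. They show that the pooled result can move from close to the planned difference to none or slightly negative, and that there is no distortion when the two effects are equal or only one kind of child is enrolled. The change is worth making because it affects what the trial can conclude; the article does not show that the result will be biased.

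**What to change.** 1. Replace the co-treatment sentence in section 2.2 with a classification of each child at treatment start: CHM only, CHM plus WM, or WM only. Record the WM class and define what counts as the same WM.
2. State in section 2.6 which contrast 53% versus 40% refers to.
3. Have the investigators name the primary contrast before outcomes are compared. The pooled comparison may be kept if that is the question they want answered.
4. Alongside any pooled comparison, report CHM plus WM versus WM, stratified by or adjusted for WM class, and CHM only versus WM as a separate contrast.

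This changes no child's treatment. It needs only wording and analysis structure, provided that the case report forms capture concurrent WM. The abstract says that treatment history is taken at baseline, so this should be confirmed.

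The cost is precision. If 25%, 50% or 75% of 250 evaluable cohort 1 children took CHM alone, about 188, 125 or 63 would remain on CHM plus WM. Against 250 in cohort 2, power for 53% versus 40% would be 77.3%, 66.6% or 46.2%, compared with 83.2% for 250 versus 250. Stratifying by WM class could thin the groups further. The report should state the lower precision of each contrast.
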